# Converting habits of antibiotic use for respiratory tract infections in German primary care – study protocol of the cluster-randomized controlled CHANGE-3 trial

**DOI:** 10.1186/s13063-019-3209-7

**Published:** 2019-02-06

**Keywords:** Antibacterial agents, Drug resistance, Drug prescriptions, Respiratory tract infections, Primary health care, Randomized controlled trial

## Abstract

**Background:**

The overuse of antibiotics is a major cause for the worldwide rise of antibiotic resistance. Although it is well known that acute respiratory tract infections (ARTI) are mainly caused by viruses and are often self limiting, antibiotics are too frequently prescribed in primary care. CHANGE-3 examines whether a complex intervention focusing on improving communication and provision of prescribing feedback reduces antibiotic use in patients suffering from ARTI.

**Methods/design:**

The CHANGE-3 trial is a cluster-randomized controlled trial nested within a web-based public campaign conducted in two regions in Germany. A total of 114 medical practices will be included. Practices randomized to the intervention will receive a practice-specific antibiotic-prescription feedback and an educational outreach visit. During the visit the whole practice team will receive an introduction to e-learning modules addressing patient-centered communication on antibiotics. Furthermore, the practices will receive tablet PCs with information on antibiotics and the treatment of ARTI to be presented to patients. Practices randomized to the control will provide care as usual. The primary outcome measure is the antibiotic prescribing rate for patients with a history of ARTI. Data collected before the intervention, during the intervention and after the intervention will be compared. The use of narrow- vs. broad-spectrum antibiotics will be analyzed as a secondary outcome. A process evaluation is also part of the trial.

**Discussion:**

This study should contribute to the growing body of research on reducing antibiotic prescription.

**Trial registration:**

ISRCTN, ISRCTN15061174. Registered retrospectively on 13 July 2018.

**Electronic supplementary material:**

The online version of this article (10.1186/s13063-019-3209-7) contains supplementary material, which is available to authorized users.

## Background

The excessive use of antibiotics in human and veterinary medicine is responsible for the worldwide rise of antibiotic resistance [1, 2]. In Germany, approximately 40–45% of all antibiotics prescribed in human medicine stem from primary care, with acute respiratory tract infections (ARTI) [3] being the most common cause. Although among both experts and non-professionals it is well known that ARTI are primarily caused by viruses and are mostly self-limiting, in too many cases antibiotics are prescribed [4–6]. The main reasons for the inadequate prescription of antibiotics in primary care include a misleading safety culture and general practitioners’ (GPs) misconception that patients would expect an antibiotic prescription [7, 8]. This leads to over-prescribing of broad-spectrum antibiotics such as quinolones and cephalosporins [3]. This eventually leads to increasing rates of antibiotic resistance, avoidable side effects and drug interactions as well as unnecessary direct and indirect costs, e.g., for hospital admissions [9–13].

Since the 1990s, efforts to reduce unnecessary antibiotic prescriptions in primary care have been made [3, 14]. Trials have proven that some interventions are able to lower medication prescription rates in a relevant manner [15, 16]. However, the effect of interventions is varying and is specific to situations and conditions [17]. A recent systematic review on interventions aiming at reducing antibiotic prescription for ARTI patients showed, for instance, positive effects of single-element and multifaceted interventions using GP communication skills’ training and point-of-care testing. Other elements, such as patient-centered information alone, had no effect [16]. Wensing et al. showed efficacy of quality circles and written feedback on professional performance and prescribing [18]. So far, most interventions focus on GPs [15, 19]. Research has shown that sensitizing the practice staff for a better interaction with patients carries the potential to relieve the GP’s work and to contribute to improved decision-making in general [20, 21]. Practice staff can play an important role in transferring knowledge to patients [21]. Thus, the idea of addressing the whole practice team in interventions to reduce unnecessary antibiotic prescriptions is gaining momentum.

## Aim

The cluster-randomized controlled CHANGE-3 trial (cRCT) aims at testing the effect of a practice intervention including practice-specific antibiotic-prescription feedback, an education outreach visit, patient-centered communication, and patient information on the rate of antibiotic prescription for ARTI in German primary care.

Patient-centered communication will be conveyed via e-learning modules. Versions for physicians and practice staff members will differ and will be target-group-specific.

For the delivery of patient information, practices will receive tablet PCs with multimedia patient information on antibiotics and the treatment of ARTI.

The cRCT is nested within a larger-scale, web-based, public campaign conducted in two German states and has the title “*Weniger Antibiotika: mehr Ideen*” (English; less antibiotics: more ideas) [22]. Whereas the campaign tests the effectiveness of informing the patient and, to some extent, health care provider information at large, the cRCT investigates whether this intensified approach produces further effects. GP practices of the control group will provide care as usual, but will have access to the web-based campaign just like the general public.

## Methods/design

### Trial design

CHANGE-3 is a two-arm cRCT with GP practices and their patients forming a cluster. It is nested within a web-based public campaign conducted in two German regions. The antibiotic prescription rates of participating GPs will be measured over two successive winter seasons (Fig. 1). Additionally, the quality of prescriptions in terms of active ingredient chosen (broad- vs. narrow-spectrum antibiotics), usage of quinolones, seasonal fluctuations, and the knowledge of patients about antibiotics and treatment of ARTI will be monitored. GP practices will be allocated randomly either to the intervention group (IG) or the control group (CG). In the latter, care will be provided as usual. Claims data from the largest German statutory health insurance provider, AOK, will be used for all analyses. The SPIRIT checklist for this protocol can be found in Additional file 1.

**Fig. 1 Fig1:**
[figure not shown]
Overview of enrollment, intervention, and assessments of the CHANGE-3 trial

### Recruitment

GP practices will be recruited in the two German states, Mecklenburg-Western Pomerania (MV) and Baden-Wurttemberg (BW). A total of 114 practices will be included in the trial (38 GPs in MV and 76 GPs in BW). GPs will be approached via invitation letters. Interested physicians will receive trial information via telephone or during a practice visit. Participating GPs will provide informed consent in writing. They will also agree to release their patients’ anonymized prescription data as stored by the German statutory health insurance provider AOK (§§295, 300 SGB V). These data include all AOK-insured patients diagnosed with ARTI who receive medical treatment during the trial. Using these data, overall and practice-specific antibiotic prescription rates will be determined.

In addition, two written patient surveys will be conducted over two successive winter seasons. In each survey participating GP practices will recruit up to 50 ARTI patients aged 17 years or over to fill in a questionnaire. The questionnaire will measure patients’ knowledge of antibiotics as well as expectations and experiences related to antibiotic prescribing. Patients’ participation in the survey will be anonymous and not related to any affiliation with a specific health insurance provider. Exclusion criteria are: not being able to read or fill in the questionnaire.

### Intervention

The intervention is multifaceted and includes different elements (Additional file 2). The IG will receive feedback on practice-specific antibiotic prescription on two occasions (Additional file 2, component 1) and an educational outreach visit (Additional file 2, component 2), which is a central focus of the intervention. During the visit, a specially trained expert will discuss the practice-specific antibiotic-prescription feedback provided in detail. Additionally, the practice will have access to e-learning modules focusing on communication strategies, e.g., on how to handle patients expecting the prescription of antibiotics (Additional file 2, component 3 and 4). Patient information on the common cold, middle ear infections, and sinus infections is tailored to different groups of patients, e.g., the elderly or parents of children with ARTI, and is provided in the form of flyers and information on tablet computers (Additional file 2, components 5 and 6). Communication designers will be involved in the development of the materials.

### Control

Patients of the CG will receive care as usual. Since the cRCT will take place during the web-based public campaign, GP practices of the CG will have access to the campaign’s materials as the general public does.

### Data collection, completeness and quality

Recruitment of GPs started in August 2017 and will continue until September 2018. The anonymized prescribing data from the GPs’ patients will be retrieved at the beginning of the trial (baseline, T0) and over two successive winter seasons: during the intensified intervention phase in the first winter season (T1) and the second winter season (T2). That means that baseline data will be retrieved retrospectively after provision of written informed consent by GPs. The intervention will start after baseline collection is completed and continue throughout the trial, due to the public campaign running in parallel. To identify participating GPs in the secondary health data from AOK, two GP identifiers will be collected (“*Lebenslange Arztnummer*”; LANR and “*Betriebsstättennummer*”; BSNR). In addition, the following information will be gathered at the start of or during the trial: age and gender of GP, time since practice setup, specialist title of GP, and practice characteristics, like number of team members and field of expertise.

Also, up to 50 patient questionnaires on patient knowledge of antibiotics and treatment of ARTI will be delivered by the GPs. Participation of ARTI patients is voluntary and anonymous. This will be done throughout the entire trial. The questionnaires will collect information on patients’ age and gender, employment situation, first language, educational background, knowledge on antibiotics, and reason for consultation. To avoid duplicates, participants who fill out the questionnaire will be listed anonymously (date of questionnaire dissemination, year of birth, and gender).

### Randomization

Participating GP practices will be randomly assigned in a 1:1 ratio into the two study groups after recruitment. Randomization will be stratified by rate of antibiotic prescription for ARTI at baseline per practice. Randomization will be performed by the Institute of Medical Biometry and Informatics at the University Hospital Heidelberg.

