### Methods to reduce bias and enhance data quality

With reference to the Cochrane Collaboration’s tool for assessing risk of bias [23], a number of procedures are carried out to reduce potential sources of bias. Firstly, to reduce selection bias, participating GP practices in both states are recruited with identical procedures. A non-responder analysis will also be performed. Secondly, randomization of participating practices will be performed electronically by statisticians not involved in physician recruitment. Thirdly, specified inclusion and exclusion criteria (ICD and ATC codes) will be used to calculate antibiotic prescription rates for ARTI among participating practices in order to reduce the risk for information bias and selective outcome reporting. Fourthly, to reduce variation in intervention delivery, outreach visits will be standardized. Due to financial and time constraints within this trial it will not be possible to blind participants and trial staff. Prior to its start, the study was registered in the public trial archive ISRCTN.

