### Statistical analyses

In a first step, descriptive statistics will be provided for the primary and secondary outcomes as well as for patient, practice, and GP characteristics, including mean, standard deviation, median, interquartile range (IQR), minimum and maximum for continuous variables, and frequency in percentages for categorical variables. The primary objective of this study is to examine the difference in antibiotic prescription rate after intervention (T1) between the two study arms.

The confirmatory analysis of the primary endpoint will be conducted based on the intention-to-treat (ITT) population, where all patients will be included in the analysis and assigned to the group they were randomized to.

A logistic mixed-effects model will be applied to assess the respective hypothesis of equal rates in both groups regarding the primary endpoint using a significance level of α = 5%. A random intercept will be included for practices. Furthermore, age and gender of patients will be included as covariates. Missing values regarding the primary endpoint will be imputed using multiple imputation. As a sensitivity analysis, the primary endpoint will be evaluated on the per-protocol population, where patients with major protocol violations will be excluded. As a further sensitivity analysis, the baseline prescription rate on practice level will be included as an additional covariate in the primary logistic mixed-effects model.

Mixed models, as described for the primary endpoint, will be used to analyze the secondary outcomes. All calculated *p* values regarding secondary endpoints will be of a descriptive nature. A detailed statistical analysis plan will be written prior to the final analysis. SAS (SAS Institute Inc., Cary, NC, USA) version 9.4 or higher will be used to carry out the analyses. A non-responder analysis is planned regarding size of practice, number of antibiotic prescriptions in case of ARTI, and application of broad-spectrum antibiotics.

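### State (MV or BW) is neither a stratification factor nor a term in the primary model, so a small, avoidable loss of precision and an unadjusted chance imbalance are accepted

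*Protocol article*

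**What the plan says.** The Recruitment section of the protocol article names both states ("GP practices will be recruited in the two German states, Mecklenburg-Western Pomerania (MV) and Baden-Wurttemberg (BW") and gives planned numbers for each: "A total of 114 practices will be included in the trial (38 GPs in MV and 76 GPs in BW". The two figures add to 114, so they are read here as practices.

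The Randomization section sets the ratio and unit ("Participating GP practices will be randomly assigned in a 1:1 ratio into the two study groups after recruitment") and names one stratification factor: "Randomization will be stratified by rate of antibiotic prescription for ARTI at baseline per practice".

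The Statistical analyses section specifies the primary logistic mixed model: "A random intercept will be included for practices", and "Furthermore, age and gender of patients will be included as covariates". One practice-level covariate appears, in a sensitivity analysis only: "the baseline prescription rate on practice level will be included as an additional covariate in the primary logistic mixed-effects model". State appears in none of these models.

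The section on reducing bias mentions the states once: "participating GP practices in both states are recruited with identical procedures". That concerns who enters the trial. It does nothing to balance the states between arms.

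**The concern.** State is known for every practice before allocation, and the sample is planned around it. Stratifying on the baseline prescribing rate balances the arms on the level before the intervention. It does not guarantee balance on anything that differs between the states later, for example the course of a winter season or use of the public campaign, and the outcome is measured in those later seasons.

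If one arm happens to hold more MV practices and the states diverge after baseline, the primary estimate moves by the difference in MV share times the state gap, and nothing in the primary model adjusts for it. What is at stake is some precision, and the awkwardness of a visible imbalance that could then be addressed only by an analysis chosen afterwards.

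**Working it through.** **The plan's own sample size (Sample size calculation section).** For 40% versus 28%, two-sided 5% and 80% power, the chi-squared formula without continuity correction gives 244 per group, as stated. The design effect is 1 + 79 × 0.2 = 16.8. Then 244 × 16.8 = 4099.2, stated as 4100, and 4099.2 / 80 = 51.24, so 52 practices per arm, 104 in all and 8320 patients. Ten more practices give 114. The figures reproduce, and nothing below changes them.

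**Chance imbalance in state.** Inputs: 114 practices, 38 of them in MV, 57 per arm. If allocation takes no account of state, the MV count X in one arm is hypergeometric:

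- Mean = 57 × 38/114 = 19.
- Variance = 57 × (1/3) × (2/3) × (57/113) = 6.39, so SD = 2.53.
- 95% range: 14 to 24.
- The arms differ in MV share by 2 × |X − 19| / 57. The probability of a split at least as uneven as 23 v 15 is 0.164, and as 24 v 14 is 0.073 (both directions counted). A difference in MV share of 10 points or more has probability 0.32.
- SD of the difference in MV share = 2 × 2.53 / 57 = 0.0887.

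**Effect on the estimate.** The planning standard error of the difference, with 4160 patients per arm, is √[(0.40 × 0.60 + 0.28 × 0.72) × 16.8 / 4160] = 0.0422, or 4.2 points. The SD of the shift is 0.0887 × gap. The gap is an assumption, shown as a range:

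| Assumed state gap (points) | SD of shift (points) | Share of variance, (SD/4.22)² | Power at 104 practices if state is adjusted for |
|---|---|---|---|
| 2 | 0.18 | 0.2% | 80.7% |
| 5 | 0.44 | 1.1% | 81.0% |
| 10 | 0.89 | 4.4% | 82.1% |
| 15 | 1.33 | 9.9% | 84.0% |

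Without adjustment, power at 104 practices is 80.7%. The power column removes the state variance, gap² × (1/3) × (2/3), from the between-practice variance 0.2 × 0.34 × 0.66 and recomputes the ICC and design effect.

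The table sets a shift computed for 114 practices against a standard error for 104. With 57 practices per arm for both, the standard error is 4.03 points and the shares for gaps of 5 and 15 points become 1.2% and 10.9%. The picture is the same.

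In an uneven allocation of 24 v 14, the shift is (10/57) × gap = 0.9, 1.8 or 2.6 points for gaps of 5, 10 or 15, against the planned effect of 12 points.

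All of this is on the risk-difference scale, as an approximation to the logistic model.

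**The case against.** The strongest reply is that nothing here is an error. Stratifying on the baseline value of the outcome is a sound choice of a strong prognostic factor, and leaving out state does not invalidate randomisation. That stands.

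A reader might infer that a surplus of one state in one arm could not be told apart from the intervention effect. The documents do not support this. Chance imbalance in a practice-level factor is ordinary sampling error, and the random practice intercept carries it into the standard error. State is known for every practice, so an imbalance can be seen and adjusted for. The sample size already allows for large variation between practices: an ICC of 0.2 at a 40% rate implies a between-practice SD of √(0.2 × 0.24) = 0.22, or 22 points. A 10-point state gap adds variance of 0.01 × 2/9 = 0.0022 against 0.048, under 5%.

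A reader might also infer that recruitment runs separately in each state under fixed quotas. The text gives only planned numbers by state and says the procedures are identical.

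A lasting difference between the states would show in the baseline rates, which are stratified on. Only divergence after baseline is left, and no figures support its size. If state and baseline rate are correlated, the hypergeometric calculation also overstates the imbalance. Both points stand, and they make the figures upper-end.

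One reply does not go through: that the matter belongs to the later analysis plan. The article states both the stratification factor and the covariates of the primary model, so this is a stated choice. The plan also expects the mixed model to explain more variance than the chi-squared test. With ICC 0.2 and 80 patients, 0.2 / (0.2 + 0.8/80) = 95% of the variance of a practice mean lies between practices. Patient age and gender reach that part only so far as case mix differs between practices.

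**Conclusion.** The point holds at low severity. Balance on state is left to chance, and the primary model does not adjust for it. The primary test remains valid, with no bias and no inflation of type I error.

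The cost is precision: for an assumed post-baseline gap of 5 to 15 points, at most about 1% to 10% of the variance of the estimate, or a gain in power from 80.7% to between 81.0% and 84.0% if state is adjusted for. At a gap of 2 points the effect is negligible.

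The conclusion rests on the planned 38/76 split being achieved, on equal arms of 57, on allocation unrelated to state, and on a state gap that the documents do not give. The case for acting is that the remedy is almost free, and that naming the term in advance avoids a dispute over post hoc adjustment if the split turns out uneven.

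**What to change.** Pre-specify state (MV/BW) as a fixed effect in the primary logistic mixed model, in the statistical analysis plan promised before the final analysis. This works whether or not allocation is complete. It costs one model parameter and no additional practices, patients or data.

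Stratify by state as well as baseline rate only if allocation has not been done. Recruitment was to end in September 2018 and the article appeared in February 2019, so it may be too late. The cost would be smaller strata, with 38 and 76 practices each divided by baseline category, which is manageable with two or three categories. If state is used in the randomisation, it should still enter the model.

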### Outcome measures

The primary outcome measure is the GPs’ antibiotic prescription rate for ARTI at the end of the trial in comparison with the baseline data. These outcome data come from routinely collected data that are provided by the German statutory health insurance provider AOK. Tables 1 and 2 summarize relevant Anatomical Therapeutic Chemical (ATC) and International Classification of Diseases (ICD) codes, respectively, for calculating antibiotic prescription rates.

**Table 1 Tab1:** Relevant Anatomical Therapeutic Chemical (ATC) codes

Drug	ATC code	Drug group	Group name
Definition of classified ATC codes	J01FA (without J01FA01)	Macrolides (without erythromycin) – *broad-spectrum antibiotics*	Macrolides
	J01DB	First-generation cephalosporins	Cephalosporins
	J01 DC	Second-generation cephalosporins	Cephalosporins
	J01DD	Third-generation cephalosporins	Cephalosporins
	J01DE	Fourth-generation cephalosporins	Cephalosporins
	J01MA	Fluoroquinolones	Gyrase inhibitors
	J01CR	Penicillins including beta-lactam inhibitors *– broad-spectrum antibiotics*	Penicillins + beta-lactam-inhibitors
	J01CA	Penicillins with extended spectrum	Penicillins with extended spectrum
	J01 CE	Beta-lactamase-sensitive penicillins	Beta-lactamase-sensitive penicillins
	J01EE01	Sulfamethoxazole and trimethoprim	Sulfamethoxazole and trimethoprim
	J01XE01	Nitrofurantoin	Trimethoprim, nitrofurantoin, fosfomycin
	J01EA01	Trimethoprim	Trimethoprim, nitrofurantoin, fosfomycin
	J01XX01	Fosfomycin	Trimethoprim, nitrofurantoin, fosfomycin
	J01FA01	Erythromycin	Erythromycin
	J01FA16	Solithromycin	Erythromycin
	J01A	Tetracyclines	Tetracyclines
	J01other	J01-other	Other antibiotics

**Table 2 Tab2:** Relevant International Classification of Diseases, version 10 (ICD-10) codes

Diagnoses	ICD-10	Indication	ICD group
Definition of classified ICD-10 codes	J20; J21.0; J21.1; J21.8; J21.9; J22; J40	Acute bronchitis	Lower respiratory infection
	J00; J02.0; J02.8; J02.9; J04; J06; J10.1; J11.1	Acute infection of the upper respiratory tract	Upper respiratory infection
	J01	Acute sinusitis	Upper respiratory infection
	J03.0; J03.8; J03.9	Tonsillitis	Upper respiratory infection
	H65.0; H65.1; H65.9; H66.0; H66.4; H66.9	Otitis media	Upper respiratory infection

The secondary outcome is the choice of active ingredient (broad- vs. narrow-spectrum) in the antibiotic prescribed.

Additionally, data for the outcomes ‘patients’ level of knowledge on antibiotics’ and ‘patients’ expectations and experiences related to antibiotic prescribing’ are collected via questionnaires in two written patient surveys. The surveys’ results are meant as a feedback to the practices about their patients’ perspective. The results of the second patient survey will show, in comparison with the first ones, whether the project interventions resulted in changes concerning patients’ expectations and patients’ knowledge. Descriptive statistics and specific tests for group comparison will be used to analyze survey data (IBM SPSS statistics 20).

